### Work package 4: cost-consequence analysis

In order to evaluate the economic effects of PDD, a cost-consequences analysis (CCA) framework will be conducted based on the various perspectives of the stakeholders. This disaggregated analysis enables the costs and consequences for each individual budget-holder to be clearly defined and presented and their own budgetary impact delineated. In this study, these stakeholders include local police forces, local health services, and members of the public.

The CCA will estimate the costs of providing the PDD intervention. We will record the quantities of resources used in each intervention area and apply local unit costs. Initial information on resource use has been collected from policing partners and local service providers alongside the TIDieR information collected for work package 1. Additional information on staff time, staffing grade, other specific resources used within the programme and overheads will be collected at the end of work package 2. Local unit costs will be applied to resource quantities to derive the total cost of providing the intervention and the cost per participant. Intervention costs will be presented for each area which will be anonymised for reporting purposes.

The CCA builds on the primary and secondary outcomes outlined in work package 3. We will estimate the treatment costs incurred by the NHS based on conditions plausibly affected by the intervention. Costs will be derived by applying national average costs to the cases identified using the NHS National Cost Collection database of unit costs (NHS England, 2022).

The social and economic costs associated with reoffending (e.g. arrests, convictions and imprisonments) as quantified in work package 3 will be included in the CCA. We will apply unit costs for each criminal justice event recorded in the data linkage. Treasury approved methods will underpin the CCA and unit costs will be extracted from the latest version of the Greater Manchester Combined Authority Unit Cost Database and the Home Office estimates of the costs of crime (GMCA Research Team, 2021; Heeks et al., 2018). This will cover the costs of crime, health and social services. Costs of crime will be presented in terms of fiscal costs and cost to society. The domains for the CCA for the 12 months following police contact are the cost of hospital admissions relating to acute mental health, alcohol and other drugs, and the criminal justice system costs of criminal conviction.

Costs will be presented in a disaggregated format which will provide clear information to the different stakeholders with respect to their financial impacts. The CCA will estimate the longer-term discounted costs over the next five years based on criminal justice contacts and health care episodes. We will construct a hybrid decision tree and Markov model based upon drug use status following PDD. The model uses the rates of post-PDD drug use, all cause death rates, and reconviction rates as transition probabilities. A mean patient cost for health care and criminal justice in each of the Markov states is applied and the simulation will be run for a period of five years. Costs and outcomes occurring beyond one year are discounted using a discount rate of 3.5% as recommended by the National Institute for Health and Clinical Excellence (NICE, 2020). We will use the NHS National Costs Collection and GMCA database combined with data from work package 3 and parameters from the published literature to estimate the return on investment. The costs of the PDD programme will also be scaled up to national level in order to estimate the overall cost of providing the intervention it if were to be nationally implemented.

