### Work package 3: quantitative outcome assessment

A quantitative outcome assessment will test hypotheses that the presence of PDD schemes in police force areas reduce adverse health and offending outcomes for drug-involved suspects. The analysis will involve comparing outcomes for cohorts of drug-involved suspects eligible for diversion in our three focus areas (i.e. police forces with PDD schemes), with those for cohorts of similar individuals in three comparison areas (i.e. forces without PDD schemes) that are in groups of police forces that are most comparable to the intervention forces (HMICFRS, 2023).

Participants in our quantitative analysis will be individuals who had contact with the police in relation to illicit drugs, who may have been eligible for diversion (regardless of whether diversion was available, offered or taken up by that individual). Each PDD and comparison police force will identify individuals who had contact with the police for a qualifying offence between 1 October and 2021 and 30 September 2022 and were aged at least 18 years. Qualifying offences will be (a) simple possession of any controlled drug (personal use), and (b) any of: shoplifting, assault, criminal damage, criminal damage without intent to commit, possession of drugs, drunk and disorderly, drunk and incapable, any theft (other than burglary); in combination with a suspected or proven offence in contravention of the Misuse of Drugs Act 1971 or the Psychoactive Substances Act 2016, in the preceding 3 years, OR a flag in police records for involvement with illicit drugs.

We will use two primary outcomes for health and reoffending:

Health—the count of hospital episodes (including unplanned/emergency inpatient admissions and emergency department visits) during the follow-up period that are related to drugs, alcohol, or accidents.Reoffending—a count of how many offences participants commit in the follow-up period, as recorded in the PNC and adjusted for the time that each participant was in the follow-up period.

We will also use the following secondary outcomes:

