Health—the measures will be (a) any entry into structured treatment for drug or alcohol use in a community setting during the follow-up period; and (b) retention in treatment for at least 28 days for those who start drug or alcohol treatment.Reoffending—(a) a dichotomous measure of any offending, with analysis offset by the duration of follow-up, and (b) a measure of the total social cost of these crimes, calculated using the costs attributed to each type of crime according to Home Office estimates of the social costs of each type of crime (Heeks et al., 2018).

The data for the quantitative impact assessment will be compiled using individual-level data linkage between databases of administrative records. Participating police forces will share lists of eligible individuals with the Department of Health and Social Care (DHSC), which is a partner in the project. The DHSC will link the data to four national health and criminal justice databases, and then pseudonymise the data before analysis within a secure data system. The four national databases will be:

The Police National Computer, which will be used to derive a measure of historical offending at study entry, and the primary and secondary reoffending outcomes;The National Drug Treatment Monitoring System, which will be used to measure secondary health outcomes (i.e. entry to and retention in drug and alcohol treatment services);Hospital Episode Statistics, which will be used to measure our primary health outcome (i.e. hospital episodes) (Herbert et al., 2017).The Office for National Statistics mortality database, which we will use to identify participants who die during the follow-up period and are to be excluded from our analysis. Deaths will only be used to censor follow-up and not as an outcome because their relative rarity would result in a lack of statistical power for detecting significant effects.

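### The 12-month hospital cost domain covers different events from the primary health outcome on which the cost-consequence analysis is said to build

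*Protocol article*

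**What the plan says.** In the protocol article, the section on work package 3 (quantitative outcome assessment) defines the primary health outcome as a count of "hospital episodes (including unplanned/emergency inpatient admissions and emergency department visits"), restricted to those "that are related to drugs, alcohol, or accidents". The secondary health outcomes are entry to structured drug or alcohol treatment, and retention in it for at least 28 days.

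The section on work package 4 (cost-consequence analysis, CCA) makes two general statements. The first ties the costing to those outcomes: "The CCA builds on the primary and secondary outcomes outlined in work package 3". The second describes its scope on the health side: "We will estimate the treatment costs incurred by the NHS based on conditions plausibly affected by the intervention". Later in the same section the domains for the 12 months after police contact are listed. The health domain is "the cost of hospital admissions relating to acute mental health, alcohol and other drugs"; the other is the criminal justice cost of conviction.

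The section then describes a five-year decision tree and Markov model organised by drug-use status after diversion: "The model uses the rates of post-PDD drug use, all cause death rates, and reconviction rates as transition probabilities". For the return on investment it names unit-cost databases, work package 3 data and published parameters as sources.

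**The concern.** A cost-consequence analysis sets costs beside outcomes so that each budget-holder can see what a change in outcome means for them. That works only if both describe the same events, or if the differences are deliberate and labelled. Here the costing claims to build on the outcomes but lists a different set of hospital events, and the article gives no reason for the difference.

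The mismatch runs in both directions. A reduction in accident-related episodes, or in emergency department visits for any of the three causes, could drive a favourable primary result and leave the 12-month health costs unchanged. A difference in acute mental health admissions, including one due to chance, would enter the costs although no work package 3 outcome examines it. The health result and the health cost could then point in different directions with no means of telling why.

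This matters beyond the article, because the Dissemination section says that reports to the funder may be used in Treasury business cases if the schemes prove effective and cost-effective.

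**Working it through.** The plan states no figure on this point, so there is none to reproduce. The check sets the two definitions side by side and then traces the input to the five-year model.

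**Step 1: compare the event sets.**

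| | Work package 3, primary health outcome | Work package 4, 12-month health domain |
|---|---|---|
| Drugs | yes | yes |
| Alcohol | yes | yes |
| Accidents | yes | no |
| Acute mental health | no | yes |
| Inpatient admissions | unplanned or emergency | hospital admissions, not limited to unplanned |
| Emergency department visits | yes | no |

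**Step 2: count the overlap.** The outcome names 3 causes and 2 settings, which gives 3 × 2 = 6 combinations. The cost domain covers drug-related and alcohol-related admissions, which is 2 of the 6. The 4 left out are accident admissions and emergency department visits for drugs, for alcohol and for accidents. One combination, acute mental health admissions, is costed without being in the outcome. These are counts of definitions, not shares of episodes.

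**Step 3: look for text that reconciles them.** The sentence on plausibly affected conditions is wide enough to cover either list, but it selects neither. The sentence listing the 12-month domains is the specific one, and it omits accidents and emergency department visits. The secondary health outcomes concern drug and alcohol treatment, so they do not bring in mental health admissions.

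**Step 4: trace the drug-use input to the five-year model.** Work package 3 gives each linked database a stated use:
- Police National Computer: offending history and reoffending.
- National Drug Treatment Monitoring System: treatment entry and retention.
- Hospital Episode Statistics: hospital episodes.
- Mortality data: deaths.

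None is assigned to measuring drug use, and drug use is not among the outcomes. Work package 2 uses type of drug use to select interviewees purposively, so it cannot yield rates for the cohorts. The remaining named source is the published literature. The article does not say that the drug-use inputs come from there, nor how a difference between PDD and comparison areas would be obtained.

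**The case against.** The best defence of the cost domain is that this kind of analysis is meant to be broad, and that a journal article may leave code lists to a fuller document. Part of this stands. Adding mental health admissions is legitimate if they are labelled as an extra domain, and missing code lists would be no fault. But breadth does not explain leaving out accidents and emergency department visits, and two stated definitions that conflict are not an omission of detail.

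Several stronger readings are tempting, but the article does not support them:

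- *Accidents and emergency visits are costed at zero throughout.* Only the 12-month domain sentence excludes them. The five-year projection refers to health care episodes generally.
- *No study dataset measures drug use, so the model rests on nothing from the study.* The fields of the treatment database are not listed, published parameters are expressly allowed, and work package 3 data are named as an input. Only the narrower point in step 4 holds.
- *Rates are entered as probabilities without conversion.* One summary sentence does not show this. A reconviction rate is often simply a proportion, and no cycle length is given.
- *Only the diverted side is modelled.* Work package 3 is comparative and feeds the return on investment; nothing says the comparison cohort is left out.
- *The model cannot have death rates because people who die are "identify participants who die during the follow-up period and are to be excluded from our analysis".* The next sentence of the article says deaths censor follow-up. Deaths are in any case identified through the linkage, and external rates could be used.

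**Conclusion.** The mismatch between the primary health outcome and the 12-month health cost domain is real, and nothing else in the article resolves it. It differs by cause (accidents out, acute mental health in) and by setting (emergency department visits out, admissions no longer limited to unplanned ones).

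Its size in money or episodes cannot be stated, because the article gives no counts by cause or setting. The conclusion rests on reading the domain sentence as the operative definition, as its wording suggests. The effect estimates in work package 3 are not touched; what suffers is the correspondence between the health effect and its cost over the first 12 months.

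The point about the five-year model is secondary. Drug-use status is a permissible basis for the model, but since it is not a study outcome, the source of its values in each group should be stated.

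**What to change.** In the section on work package 4, redefine the 12-month health domain as the cost of the work package 3 primary-outcome events: drug, alcohol and accident episodes, both emergency inpatient and emergency department, in the PDD and the comparison cohorts alike. If acute mental health admissions are kept, report them as a separately labelled additional domain, and say that an admission qualifying under both headings is counted once.

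For the five-year model, add a sentence saying whether the drug-use inputs come from the published literature, and how a difference in drug use between PDD and comparison areas would be obtained.

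The cost is small. The primary-outcome events are already to be linked, so this means a little more costing work and, if mental health is kept, a slightly wider hospital data extract.

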## The evaluated PDD schemes

In collaboration with local stakeholders and based on Hoffmann et al.’s (2014) template for intervention description and replication (TIDieR) checklist, we have developed manuals which describe the operation of each of the PDD schemes in the three focus areas: Durham (Hendrie et al. (2023a), Thames Valley (Hendrie et al. (2023b) and the West Midlands (Hendrie et al. (2023c). Their common features are that they involve police contact with people who use drugs who are suspected of committing an offence (e.g. drug possession). We refer to this target group as ‘drug-involved suspects’. In each area, PDD involves diversion to group or individual sessions of drug education and advice instead of proceeding with prosecution for the suspected offence. People who are diverted may also be referred to other services (e.g. local drug treatment agencies) if needed. There are some differences between the three focus areas. In the West Midlands and Thames Valley, the interventions to which people are diverted are provided by third sector organisations and people generally receive online or face-to-face drug education sessions. Eligibility in these areas is confined to people suspected of simple drug possession (with no intent to supply). In Durham, the eligibility criteria include a wider range of offences. Here, the diversion takes the form of one-to-one meetings with staff employed by the police (known as ‘navigators’). These similarities and differences will be studied in our evaluation to examine the various mechanisms and outcomes which they trigger.

The overall study design is a mixed methods realist evaluation which combines a: qualitative assessment of the implementation, contexts, mechanisms, moderators and outcomes of the evaluated PDD schemes; with a quantitative, quasi-experimental analysis of administrative data on the effects of being exposed to the presence of PDD schemes on reoffending and health outcomes. These will be supplemented with analysis of the cost-consequences of the evaluated PDD schemes, an analysis of the equity of their implementation and effects, and a realist synthesis of the various findings from these different methods.

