This theory of change was based on the programme theory provided by Stevens et al.’s (2022) realist review of alternatives to criminalisation for drug possession, with additional input from research published since the search was carried out for this review (in 2018). This additional research was found using similar search terms and databases to those used in the original review. The theory was further developed through discussion with stakeholders at the local and national workshops. The resulting theory of change is available online as a separate document (Stevens et al., 2023). In summary, it suggests that PDD may have positive effects on offending and health outcomes via two causal pathways. One is avoidance of the negative effects of criminalisation. The other is enhancing the support and treatment available to people who are at risk of drug-related offending and health harms. The theory of change also identifies a range of relevant contexts and moderators of the outcomes of PDD, as displayed in Fig. 1.

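### The 12-month cost domains leave out structured drug and alcohol treatment, which diversion is meant to increase, and conflict with the wider costing statements around them

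*Protocol article*

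**What the plan says.** Under Work package 4, the article states the domains outright: "The domains for the CCA for the 12 months following police contact are the cost of hospital admissions relating to acute mental health". The sentence runs on, so that the list in full is the cost of hospital admissions "relating to acute mental health, alcohol and other drugs, and the criminal justice system costs of criminal conviction". No community treatment appears.

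Other parts of the article make treatment central or give the costing a wider reach:

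- **Theory of change (Work package 1).** Of the two causal pathways, one is avoiding the harms of criminalisation. "The other is enhancing the support and treatment available to people who are at risk of drug-related offending and health harms".
- **The evaluated PDD schemes.** "People who are diverted may also be referred to other services (e.g. local drug treatment agencies) if needed".
- **Secondary health outcomes (Work package 3).** The first is "any entry into structured treatment for drug or alcohol use in a community setting during the follow-up period"; the second is retention for at least 28 days among those who start. Both come from the National Drug Treatment Monitoring System, "which will be used to measure secondary health outcomes (i.e. entry to and retention in drug and alcohol treatment services").
- **Scope of the CCA (Work package 4).** "The CCA builds on the primary and secondary outcomes outlined in work package 3". The section also promises to estimate NHS treatment costs for conditions that the scheme might plausibly influence. Of the unit costs it says: "This will cover the costs of crime, health and social services".
- **Programme cost (Work package 4).** This covers the resources used to deliver the scheme itself, such as staff time, grade and overheads.

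**The concern.** The domain list is worded as complete: it says what the domains are, not what they include. Read that way, it counts two places where PDD could save money (admissions and convictions) and leaves out one where PDD is designed to raise spending. Programme costing does not fill the gap, because onward treatment is described as a separate service to which people may be referred.

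The CCA promises a disaggregated account in which each budget-holder can see its own impact. Under the list as written, whoever pays for community treatment would see no entry for it. The section also promises a return on investment, which does combine costs and savings. The Dissemination section says that reports from the evaluation may support business cases for more spending on PDD, so the scope of costs matters to the decision.

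**Working it through.** The article gives no figure to reproduce here, so the check is mainly a comparison of text.

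**1. The list against the rest of the article**

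| Item | Elsewhere in the article | In the 12-month list? |
|---|---|---|
| Structured drug and alcohol treatment | Causal pathway; secondary outcomes; linked records | No |
| Arrests and imprisonments | Given as examples of reoffending costs in the CCA (Work package 4) | No, conviction only |
| Emergency department visits | Part of the primary health outcome (Work package 3) | No, admissions only |
| Accident-related episodes | Part of the primary health outcome (Work package 3) | No |
| Social services | Unit costs said to cover them (Work package 4) | No |

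The list is therefore narrower than its surroundings in several respects. Treatment is the one item in the table that the theory of change expects PDD to increase.

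**2. Whether a wider sentence settles the matter.** Three could be read to include treatment: the one building the CCA on the secondary outcomes, the one on NHS treatment costs, and the one on crime, health and social services. None names community drug or alcohol treatment as a costed item, and nothing says which statement takes precedence over the list.

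**3. Direction, if the list governs.** Let d be the difference in the proportion of eligible suspects entering treatment (PDD minus comparison areas) and c the mean cost per entrant. The omitted cost per eligible suspect is

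t = d × c.

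It is positive whenever PDD raises entry, and changes sign if PDD lowers it.

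**4. Effect on a return on investment.** The article does not define the ratio. Take the usual form (S − C)/C, with savings S and programme cost C, both positive. With t included:

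- netted against savings: (S − t − C)/C, which is lower by t/C;
- added to cost: (S − C − t)/(C + t) = S/(C + t) − 1, which is below S/C − 1.

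Either way, leaving out a positive t overstates the return.

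**5. Size.** The article states neither d nor c. Purely as an illustration, with both inputs assumed:

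- 0.03 × £1,000 = £30
- 0.05 × £2,000 = £100
- 0.10 × £4,000 = £400 per eligible suspect

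These show how the formula behaves. They are not estimates and say nothing about materiality, because the article gives no programme cost or saving to set them against.

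**The case against.** The strongest reply is that silence in one sentence is not exclusion. The CCA is said to build on the secondary outcomes, which are treatment outcomes on the health side, and to estimate NHS treatment costs. The list also drops arrests and imprisonments, which looks more like loose summary wording than selection in favour of PDD. This stands as far as it goes: a reader might infer that PDD will definitely not be charged for treatment, and the article does not support that. What it shows is a conflict over scope.

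The five-year model has its own stated basis (contacts with the justice system and episodes of health care), and the return on investment draws on Work package 3 data. The 12-month limits therefore need not carry over. This also stands, so any effect on the return on investment is conditional.

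Three further inferences should be resisted:

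- **National scale-up.** It is defined as the cost of providing the programme, so a missing downstream domain does not bias it.
- **Net cost per participant.** This is not a stated output. The cost per participant in the article is a delivery cost.
- **Treatment as the main downstream cost, and all savings as its benefit.** Referral is made only if needed, two of the three schemes are confined to simple possession and generally deliver education sessions, and the other pathway is avoiding criminalisation.

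Finally, an article may leave itemised costing to a fuller plan. That would answer a complaint about missing detail. It does not answer this point, because the article itself states the domains and does so in a way that conflicts with its other sentences.

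**Conclusion.** The point holds as a scope conflict with a conditional bias. The stated 12-month domains omit a cost that PDD is intended to raise and that the study already measures in part, while neighbouring sentences promise wider coverage.

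Two conditions are needed for the 12-month budget impact to be one-sided: the list is followed as written, and PDD raises treatment entry. A third is needed for the return on investment to be overstated: the same scope is carried into it. Given those conditions the direction favours PDD. The size cannot be established from the article. The correction is worth making because the text can be fixed before the analysis and the treatment records are already to be linked.

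**What to change.** - Add structured drug and alcohol treatment as a named 12-month domain. Cost it from the linked treatment monitoring records, using entry and retention, or time in treatment if that is extracted, over the same 12 months as the other domains.
- Apply it to all eligible suspects in both PDD and comparison areas, state the unit cost and its source, and show it under the budget-holder that pays.
- Include it explicitly in the health care costs of the five-year model and in the return on investment.
- Reconcile the domain list with the wider statements on secondary outcomes, NHS treatment costs, social services, and arrests and imprisonments, and say which list governs.

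The cost is a little extra costing work. Entry and retention are already planned measures, but the article does not say that time in treatment will be extracted or identify a unit cost for treatment, so those two items need confirming. The return on investment may come out less favourable.

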## Background

There is increasing interest in the use of police drug diversion (PDD) schemes. Following the review by Stevens et al. (2022), we define such schemes as alternatives to criminalisation for minor drug-related offences, including—but not limited to—simple possession for personal use. They are alternatives that provide people suspected of such offences with an educative or therapeutic intervention, rather than being processed through prosecution and conviction. Such diversion has a long history in English policing, going back at least to the 1930s,^1^ but its use for drug offences was not openly acknowledged until more recently. Several police forces in the UK and elsewhere are now operating such schemes (Shaw et al., 2022; Stevens et al., 2022). Their use is likely to expand as the government drives policy on ‘out-of-court disposals’ (OOCDs), as signalled in the White Paper on a *Smarter Approach to Sentencing* (MoJ, 2020) and by the subsequent Police, Crime, Sentencing and Courts Act 2022. OOCDs include a range of disposals available for use by the police in England and Wales which enable police officers to resolve cases without suspects being charged or prosecuted, of which PDD is one form (Shaw et al., 2022).

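### The five-year cost model takes reconviction as its only crime-related transition, although work package 3 measures offences and diversion can lower conviction without lowering offending

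*Protocol article*

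**What the plan says.** All references are to the Protocol article.

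- **Work package 4, starting point.** "The CCA builds on the primary and secondary outcomes outlined in work package 3".
- **Work package 3, reoffending outcomes.** The primary outcome is "a count of how many offences participants commit in the follow-up period", taken from the Police National Computer. The secondary outcomes are any offending and the total social cost of the crimes, priced by crime type. Reconviction is not among them.
- **Work package 4, basis of the five-year costs.** The analysis estimates "longer-term discounted costs over the next five years based on criminal justice contacts and health care episodes".
- **Work package 4, structure.** "We will construct a hybrid decision tree and Markov model based upon drug use status following PDD". Each state receives a mean health care and criminal justice cost.
- **Work package 4, transitions.** "The model uses the rates of post-PDD drug use, all cause death rates, and reconviction rates as transition probabilities".
- **Work package 4, other crime costing.** Unit costs are applied to every criminal justice event in the linked data. The 12-month justice domain, however, names only the cost of conviction. On reporting: "Costs of crime will be presented in terms of fiscal costs and cost to society".
- **Background, definition of PDD.** Suspects receive an educative or therapeutic intervention "rather than being processed through prosecution and conviction".
- **The evaluated PDD schemes, eligibility.** In the West Midlands and Thames Valley only simple possession can be diverted. Durham accepts a wider range of offences.

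**The concern.** A repeat offence that is diverted again, or otherwise settled out of court, is an offence and a police contact but not a conviction. Conviction is thus a measure of repeat crime that the intervention acts on directly, apart from any effect on behaviour. Used to compare PDD areas with comparison areas, it can mix two things: people offending less, and the same offending being dealt with differently.

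The distinction matters most for cost to society. Court and prison costs do depend on conviction, so avoiding convictions saves that money. The social cost of a crime arises from the crime, whatever the disposal.

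The model contributes to a return-on-investment estimate. The Dissemination section says that reports to the funder may support business cases to the Treasury. A saving that came partly from relabelling disposals would be hard to detect at that stage.

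**Working it through.** The plan gives no reconviction rate, diverted share or modelled saving, so it has no figure to reproduce. The check sets the units of crime side by side and then shows, under assumed shares, how far a conviction-based measure could move.

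**1. Units of crime in the plan**

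| Place | Unit |
|---|---|
| Work package 3, primary reoffending outcome | offences |
| Work package 3, secondary reoffending outcomes | any offending; social cost by crime type |
| Work package 4, five-year costs | criminal justice contacts |
| Work package 4, unit costing | each criminal justice event |
| Work package 4, 12-month justice domain | conviction |
| Work package 4, model transitions | reconviction |

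The last two rows are narrower than the rest, and the text does not connect them.

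**2. Formula**

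Let r be the true ratio of repeat offences (PDD to comparison), and let c1 and c0 be the shares of repeat offences ending in conviction in PDD and comparison areas. Then:

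- conviction-based ratio = r × c1/c0
- apparent saving = 1 − r × c1/c0
- true saving = 1 − r

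**3. Results (all ratios are assumptions)**

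| r | c1/c0 | True saving | Apparent saving |
|---|---|---|---|
| 1.00 | 1.00 | 0% | 0% |
| 1.00 | 0.90 | 0% | 10% |
| 1.00 | 0.80 | 0% | 20% |
| 1.00 | 0.70 | 0% | 30% |
| 0.90 | 0.80 | 10% | 1 − 0.72 = 28% |
| 1.10 | 0.80 | −10% | 1 − 0.88 = 12% |

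In the last row a true 10% rise in offending appears as a 12% saving, so the sign can reverse. With offences as the input, r = 1.00 gives 0% whatever share is diverted.

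**4. Allowing for limited eligibility**

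Let s be the share of repeat convictions that PDD could divert, and d the fraction of those actually diverted in excess of the comparison areas. With r = 1, the apparent saving is s × d.

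| s | d = 0.25 | d = 0.50 | d = 0.75 |
|---|---|---|---|
| 0.2 | 5% | 10% | 15% |
| 0.5 | 12.5% | 25% | 37.5% |

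A low s is the more natural assumption where only simple possession is divertible.

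**5. Discounting**

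With the first year undiscounted and 3.5% thereafter, the five-year sum is 1 + 1/1.035 + 1/1.035² + 1/1.035³ + 1/1.035⁴ = 4.67. With constant annual rates it multiplies both sides equally and cancels in the percentages, so it adds no evidence about the bias.

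**The case against.** A reader might infer that reconviction drives the whole model, that crimes settled without conviction drop out of it, and that the crime saving is therefore overstated. The documents do not support that reading, for these reasons:

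- **Structure.** The model is built on drug use status, and reconviction is one of three transition inputs. Parameters may also come from the literature. If reconviction rates depended on drug use state and were shared by both sides, the PDD effect would run through drug use and no conviction artefact would arise.
- **State costs.** A mean criminal justice cost per state, with five-year costs "based on criminal justice contacts and health care episodes", could include arrests, diversions and other disposals.
- **Societal cost.** The plan does not say that cost to society follows reconviction inside the model. Work package 3 already prices offences socially over the observed follow-up, and work package 4 draws on those data.
- **Size.** In two of three areas only simple possession is divertible. The Background presents out-of-court disposals as available to police across England and Wales, so only the excess in PDD areas counts. The main comparison also includes eligible people never offered diversion, which dilutes that excess.
- **Direction.** Work package 5 plans to look for net-widening, which could raise penal contact in PDD areas.

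These points stand, and they make the bias conditional. They do not remove the defect. Reconviction as a transition and conviction as the 12-month justice domain are stated choices, not details left to a fuller plan. Inclusive state costs are only a partial answer: modelled cost is state cost multiplied by time in state, and transitions set that time. If reconviction moves people between states, a lower conviction share in PDD areas changes the cost total even when each state's mean cost covers all contacts.

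**Conclusion.** The concern holds in a limited form. The plan names, as the model's only crime-related transition, an event that is not a work package 3 outcome and that PDD can lower by design. It also uses contacts, events and convictions in the same section without reconciling them.

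The model would credit PDD with a fall in repeat crime that had not occurred if two conditions hold: repeat offences end in conviction less often in PDD than in comparison areas, and modelled crime or cost to society follows reconviction. The plan establishes neither. The 10% to 30% range illustrates assumed ratios and is not an estimate. The effect is probably limited mainly to repeat possession in the West Midlands and Thames Valley, and could reach other offence types in Durham.

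The point concerns cost to society and any reading of the result as less crime. It does not touch the fiscal saving from fewer convictions, which is real.

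**What to change.** In work package 4:

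1. Use the work package 3 offence outcomes (offence rate or any offending, whatever the disposal) for the reoffending transition.
2. Attach cost to society to offences in the five-year model, as work package 3 already does for the observed follow-up.
3. Use conviction only to trigger court and prison costs, and cost diversion and other out-of-court disposals separately as fiscal costs. Widen the 12-month justice domain to match.
4. Reconcile the terms criminal justice contacts, criminal justice event, criminal conviction and reconviction rates, stating which event carries which cost.

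The cost is a change of wording and some extra tabulation of offences by disposal. This assumes that the linked police data hold offences settled without conviction; the article does not say, so it should be confirmed. The modelled saving may become less favourable.
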